### Questionnaires administration

The fatigue numerical rating scale will be used to assess the severity of fatigue experienced by patients, while the MRC dyspnoea scale will be used to evaluate breathlessness. Quality of life will be assessed using the EQ5D-5L tool, which consists of the EQ-5D descriptive system and the EQ visual analogue scale (EQ-VAS). The HADS will be used to evaluate symptoms of anxiety and depression, while the PCL-5 will be used for first screening for PTSD and monitoring symptoms change during time. The MOCA will be used to assess cognitive function, and the WHODAS 2.0 will be used to measure health and disabilities in clinical practice. All questionnaires with the relative scores and the CRF will be listed in Table 2 and more detailed information attached as supplementary documents (Supplementary Appendix).

**Table 2 Tab2:** Presenting the questionnaires administered to enrolled patients, along with information regarding their scoring

Administered questionnaires	
**Score**	**Levels/range**
Symptom assessment with COVID-19 WHO CRF	-Yes, but not present anymore
	-Yes, still present
	-Yes, intermittent
	-No
	-Unknown
Fatigue Numerical Rating Scale Fatigue Severity Scale	Likert Scale from 1 to 7
	Likert Scale from 0 to 10
Modified Medical Research Council (MRC) Dyspnoea Scale	Likert Scale from 0 to 4
Comorbidity relapse or new comorbidity	-Yes
	-No
	-If yes, type of comorbidity and date of diagnosis
Hospital re-admission	-Yes
	-No
	-If yes, reason and date of re-admission
QoL (EQ5D-5L)	Likert scale from 1 to 5
	Scale from 0 to 100
Hospital Anxiety and Depression Scale (HADS-A/D)	Score Depression from 0 to 21
	Score Anxiety from 0 to 21
	(0–7 normal, 8–10 borderline, 11–21 patological)
Post Traumatic Stress Disorders (PTSD) checklist for DSM-5 (PCL-5)	Score from 0 to 80
Montreal Cognitive Assessment (MOCA)	Score from 0 to 30 (adjusted for age and education) (≥ 26 no cognitive impairment; < 26 cognitive impairment
Functioning (WHODAS)	Score from 0 to 100

Legend: WHO CRF, WHO’s Post COVID case report form (constitutional, respiratory, cardiac, neurological, digestive, muscoloskeletal, ear/nose/throat, psychological, psychiatric symptoms; dermatologic, renal, endocrine, haematologic, autoimmune manifestations); MRC dyspnoea scale, Modified Medical Research Council Dyspnoea Scale; QoL (EQ5D-5L), quality of life (5-level EQ-5D version); MOCA, Montreal Cognitive Assessment; HADS-A/D, Hospital Anxiety and Depression Scale; PCL-5, Post Traumatic Stress Disorders (PTSD) checklist for DSM-5; WHODAS, World Health Organization Disability Assessment schedule 2.0, 12-item version

### Biological samples collection

The study protocol includes collection of biological samples for hospitalised COVID-19 patients during the acute phase. Blood samples and a nasopharyngeal swab will be collected at hospital admission for assessment of SARS-CoV-2 diagnostics, viral variant and viral sequencing, and cellular immunity. Blood samples will also be collected at different time points after enrolment in the post-COVID-19 cohort for the same analysis as in the acute phase. Whole blood samples will be stored, centrifuged, and separated into plasma, and peripheral blood mononuclear cells will be separated for immunological and viral analysis. Samples will be shipped to the University of Siena, Italy, for SARS-CoV-2 neutralising antibodies and for assessment of neutralisation assays, and to Karolinska Institutet, Sweden, for neutralisation assays and for assessment of SARS-CoV-2 diagnostics (WP2 of EuCare Project). The shipment of samples will follow specific regulations and procedures for packaging and international transport. All stored samples will be analysed and destroyed in accordance with current legal and ethical requirements.

### Data collection

During the acute phase of COVID-19 disease, data collection involves gathering demographic, clinical, and viro-immunological data. Subsequently, data collection is requested at each follow-up time point. To facilitate this process, a specially designed data management suite has been implemented. It incorporates a security-focused architecture that enables manual data entry into case report forms and secure file transfer for bulk data uploads. This flexible approach accommodates the various data infrastructures employed by the participating centres, whether they collect data from databases or manually. All data is meticulously curated and consolidated within a centralised relational database.

Data collection procedures strictly adhere to the established protocol, the most recent version of the Declaration of Helsinki, the International Conference on Harmonization Good Clinical Practice (ICH-GCP) or ISO EN 14155 guidelines, the regulation 2016/679 GDPR, as well as all relevant national legal and regulatory requirements.

### Data analysis

The study data will be presented as absolute numbers and percentages for categorical data, median and Interquartile Range or mean and standard deviation for quantitative variables. The incidence of post-COVID-19 condition will be calculated, and comparison between groups based on exposure factors of interest will be performed using appropriate statistical tests such as Student t-test or Mann Whitney and Chi-square test. Predictors of post COVID-19 condition will be investigated by fitting a univariable and multivariable logistic regression analysis which will be adjusted for possible confounders.

Due to potential losses to follow-up, not all hospitalised COVID-19 patients and patients diagnosed with SARS-CoV-2 infection will attend the post COVID-19 visit. This may result in a non-representative sample, potentially leading to collider bias and distorting the estimation of the effect of an exposure of interest. This bias can be addressed for hospitalised patients by using Inverse Probability Weighting through the creation of a pseudo-sample where individuals are weighted according to the inverse of the probability of being sampled for the post COVID-19 visit. A multivariable logistic regression model will be fitted to estimate the probability of COVID-19 hospitalised individuals to be included in the post COVID-19 cohort based on their characteristics (propensity score, PS), and weights inversely proportional to this probability will be generated (1/PS). Weighted logistic regression analyses will then be used to investigate predictors of post COVID-19 condition. Missing data will be handled using the missing “indicator method,” or alternatively using multiple imputations technique.

The sample size calculation will be determined by the number of expected events in the follow-up period. Based on the currently available data, we estimated an incidence of WHO post COVID-19 condition of 54% (95%CI 45–69%). We will use the comparison between the risk of developing post-COVID-19 condition in participants infected with the Delta versus Omicron viral variant of concern (VoC) for the sample size calculation. According to recent analysis, after controlling for vaccination and other confounders, the risk of hospitalisation comparing Omicron versus Delta variant ranged between 0.55 and 0.88 [21]. Our assumption is that if post COVID-19 condition occurs due to the direct effects of the virus (e.g., through disease severity, level of hyper-inflammation, or other), a similar difference could be seen when comparing the long-term risk of developing post COVID-19 condition by VoC. The cohort of 2,300 participants, accounting for 35% of follow-up, will still guarantee 90% power to detect a reduction in the risk of post-acute sequelae of at least 25% comparing participants infected with Omicron vs. Delta variants.

Data handling and statistical analyses will be performed by the team of statisticians and Artificial Intelligence experts in WP5. Python computing will be used for executing the statistical analysis.

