### Study objectives

The primary objective of the study is to assess the incidence and risk factors of post-COVID-19 condition in a cohort of recovered COVID-19 patients.

The secondary objectives of the study are as follows:To evaluate the association between circulating SARS-CoV-2 variants and the risk of post-COVID-19 condition.To identify different clinical phenotypes of post-COVID-19 condition.To evaluate the long-term residual organ impairment, specifically of the lung, heart, central nervous system, and peripheral nervous system, in relation to patient demographic and clinical characteristics such as age, gender, comorbidities, severity of disease, and virology including viral variant, specific mutations, and viral load in the acute phase.To compare the incidence of post COVID-19 condition between males and females.

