## Possible study strengths and limitations

The strengths of this medical study include its international cohort of patients who will be followed-up for one year after acute infection. The study also collects a comprehensive list of symptoms and objective measures of symptoms, such as dyspnoea, fatigue, and psychological issues, through standardised questionnaires and scales. Additionally, blood samples will be collected during the acute phase and follow-up for future studies on possible pathogenetic mechanisms of post COVID-19 condition.

However, there are also some potential limitations of the study to consider. One possible limitation is the risk of selection bias, as patients without ongoing symptoms may not keep follow-up appointments, leading to losses in follow-up, despite some statistical methods could be used to handle this bias. Another possible limitation is the potential overestimation of post COVID-19 condition due to the WHO definition, which includes any kind of symptom.

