The comprehensive questionnaires for symptom collection and the scales for the objective and standardised measure of symptoms such as dyspnoea, fatigue, and psychological issues (anxiety, depression, PTSD, and health-related quality of life) will be repeated at different time points, allowing us to understand the duration and evolution of symptoms over time. Through questionnaires, data about vaccination against SARS CoV-2, reinfections, and new health problems requiring hospital admission or new diagnosis after COVID-19, such as the new onset of diabetes or other health conditions, will be collected.

The collection of biological samples will allow future studies on pathogenetic mechanisms of post-COVID-19 sequelae, such as persistent or excessive inflammation, immune dysregulation, or viral reservoirs.

The strengths of this study protocol are the inclusion of several cohorts outside Europe and the long study period that allows a clear and wide overview of the post COVID-19 condition. We also need to recognise that the study has some limitations, as already stated. Possible solutions to overcome these limitations could be the use of statistical methods such as propensity score matching to address biases due to losses of follow-up. The telehealth approach that is currently being implemented at the coordinating centre for performing post-COVID-19 evaluations without coming to the hospital could reduce losses to follow-up.

In conclusion, the EuCARE-POSTCOVID Study is an international multicentre cohort study that aims to better define and characterise the post COVID-19 condition over the different pandemic waves. The comprehension of the current epidemiology, predictors, clinical manifestations, and pathogenetic mechanisms of this syndrome is crucial in delineating the best management and therapeutic approaches that could improve patients' quality of life.

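### Inverse probability weighting for non-attendance is planned only for hospitalised patients and only in the predictor regressions; incidence, part of the primary objective, has no stated correction or sensitivity analysis

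*Protocol article*

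**What the plan says.** Under Study objectives, incidence stands first: "The primary objective of the study is to assess the incidence and risk factors of post-COVID-19 condition". Under Data analysis, the stated plan for it is "The incidence of post-COVID-19 condition will be calculated, and comparison between groups based on exposure factors of interest", the comparison being made with simple tests. No weighting, bound or sensitivity analysis is attached to that figure.

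The same section recognises the attendance problem in both populations: "not all hospitalised COVID-19 patients and patients diagnosed with SARS-CoV-2 infection will attend the post COVID-19 visit". It describes the harm as "potentially leading to collider bias and distorting the estimation of the effect of an exposure of interest", so distortion of the incidence itself is not named. The remedy is narrower than the problem: "This bias can be addressed for hospitalised patients by using Inverse Probability Weighting". The weights are the inverse of a modelled probability of inclusion, based on the characteristics of hospitalised individuals. Their use is fixed as follows: "Weighted logistic regression analyses will then be used to investigate predictors of post COVID-19 condition".

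Under Possible study strengths and limitations, the article gives a specific reason for non-attendance: "patients without ongoing symptoms may not keep follow-up appointments, leading to losses in follow-up". It adds only that statistical methods could be used. The Discussion names a different method from the analysis section: "the use of statistical methods such as propensity score matching to address biases due to losses of follow-up".

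**The concern.** The attendance mechanism that the protocol names is selection on the outcome. If people who feel well come back less often, the proportion with symptoms among those seen exceeds the proportion among all who recovered. That acts directly on incidence. Yet the only specified correction is directed at exposure effects, and at one of the two patient groups.

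There are two gaps. The first is coverage: the incidence in both groups, and every analysis in outpatients, is left without a stated correction. The second is adequacy: weights built on patient characteristics can correct for attendance that depends on those characteristics, but not for attendance that depends on the symptoms themselves once those characteristics are accounted for.

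At stake is the headline incidence. The article already concedes that the WHO definition may overestimate the condition, and selective attendance would push in the same direction.

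**Working it through.** **Inputs from the protocol article (sample-size paragraph of Data analysis).** Expected incidence 54% (95% CI 45–69%); cohort of 2,300; 35% for follow-up. The wording of the 35% is unclear. I read it as 35% lost, so 2,300 × 0.65 = 1,495 are seen.

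**Assumption.** The documents give no attendance by symptom status. Let r be attendance of symptomatic patients divided by attendance of symptom-free patients. I use r = 1.25 to 2.

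**The plan's own computed figure.** The section gives no figure for bias in incidence. Its one computed result is 90% power for Omicron versus Delta. With 54% versus 40.5% (a 25% reduction), two-sided 5% (assumed) and 1,495 people, an equal split gives 99.95% power, and a 10:90 split gives about 89%. The split and alpha are not stated, so the 90% can be neither confirmed nor refuted. Nothing below depends on it.

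**Step 1: incidence among attenders.** With true incidence I, the observed proportion is I·r / (I·r + 1 − I). Symptom-free attendance is 0.65 / (I·r + 1 − I), and symptomatic attendance is r times that. For I = 0.54:

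| r | Attendance, symptomatic / symptom-free | Calculation | Observed incidence |
|---|---|---|---|
| 1.25 | 72% / 57% | 0.675 / 1.135 | 59.5% |
| 1.5 | 77% / 51% | 0.810 / 1.270 | 63.8% |
| 2 | 84% / 42% | 1.080 / 1.540 | 70.1% |

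The overestimate is 5 to 16 points.

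**Step 2: the reverse.** If 54% is observed, the true incidence is (0.54/r) / (0.54/r + 0.46). This gives 48.4%, 43.9% and 37.0% for r = 1.25, 1.5 and 2.

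**Step 3: bounds without an assumption on attendance by symptoms.** With 54% observed and 35% unseen:
- lower bound, all unseen symptom-free: 0.65 × 0.54 = 35.1%;
- upper bound, all unseen symptomatic: 35.1% + 35% = 70.1%.

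Sampling error for comparison: 1.96 × √(0.54 × 0.46 / 1,495) = 2.5 points either way.

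If the 35% meant the share retained, the bounds would be 0.35 × 0.54 = 18.9% to 18.9% + 65% = 83.9%, which is wider still.

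**Step 4: would the planned type of weight be enough?** Take an invented binary characteristic, present in half the patients, with incidence 44% without it and 64% with it, so 54% overall.
- Attendance depends on the characteristic (50% without, 80% with). Unweighted: (0.5 × 0.44 × 0.50 + 0.5 × 0.64 × 0.80) / 0.65 = 56.3%. Weighted: 54.0%, the truth.
- Attendance depends on symptoms (77% with, 51% without). Unweighted: 0.54 × 0.77 / (0.54 × 0.77 + 0.46 × 0.51) = 63.9%. Weighted: the mean of the stratum values among attenders, (54.3% + 72.9%) / 2 = 63.6%.

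Weighting removes the bias in the first case and hardly touches it in the second. Extending the existing weights to incidence is therefore useful but not sufficient.

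**The case against.** The best defence has four parts.

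- **Silence is not exclusion.** The text does not say that incidence will be unweighted, and this is a condensed article whose analysis plan is not shown. That stands for details such as the variance method. It does not dispose of the point: the article itself states the problem for two populations and then assigns the remedy to one population and one analysis.
- **The limitation is disclosed and partly mitigated.** The article admits possible selection bias, allows questionnaires by phone for patients unable to attend, and describes telehealth being introduced at the coordinating centre. This stands and lowers the severity. These measures may reduce losses, but they do not say how the remaining losses enter the incidence estimate.
- **Outpatients may have no denominator.** The article describes an acute-phase source cohort only for hospitalised patients, so weights for outpatients may be impossible. This stands. It calls for a label and bounds rather than weights.
- **The matching remark is tentative.** It appears in the Discussion as a possible solution. That is fair, and the request is only that it be reconciled with the analysis section.

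A reader might infer more than the documents support:

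- *That incidence will be biased upwards.* The article says symptom-free patients may not attend, and gives no attendance by symptoms.
- *That the variant contrast in hospitalised patients certainly carries collider bias, since variant affects hospitalisation.* That needs uncontrolled common causes of hospitalisation and outcome. The plan includes confounder adjustment, and the size cannot be derived from the text.
- *That the weighted tests have an inflated type I error.* The variance method is not stated. The 2,300 and 1,495 describe the whole cohort, not the hospitalised patients to whom the weights apply.

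**Conclusion.** The point holds as a change that should be made. As written, the plan attaches its only attendance correction to predictor models in hospitalised patients, and leaves incidence in both groups without a stated correction or sensitivity analysis. The article's own account of who may stay away makes an upward bias in incidence plausible.

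The size is illustrative. A true 54% would be seen as about 60% to 70% if symptomatic patients attend 1.25 to 2 times as often, with 65% attending overall. Without any assumption on attendance by symptoms, the range for an observed 54% is 35% to 70%, far wider than the ±2.5 points of sampling error. These figures rest on reading the 35% as loss and on applying it to the whole cohort. The fraction of hospitalised patients who enter the post-COVID cohort is not given and may differ.

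That incidence is unweighted is a conclusion from the stated scope of the weights, not from an explicit sentence.

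**What to change.** 1. Report incidence separately for hospitalised patients and outpatients. For hospitalised patients, give the weighted beside the unweighted figure, with robust or bootstrap intervals.
2. Label outpatient incidence *among attenders*, unless a denominator of diagnosed outpatients exists from which weights can be built.
3. Because weights on acute-phase characteristics cannot remove selection on symptoms, add a delta-adjusted analysis and best/worst-case bounds in each group where a denominator is known. Inform the delta values with phone questionnaires, which the protocol already allows for patients unable to attend.
4. Reconcile the Discussion, which names propensity score matching for losses to follow-up, with the Data analysis section, which names weighting.

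The cost is wording, programming and some phone contacts of a kind already permitted. The sponsor would also have to present a wider and less favourable incidence range.

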### Patient assessment and follow-up protocol

The patient assessment and follow-up protocol for acute COVID-19 disease involves follow-up visits at 2–3, 6–9, and 12–15 months after clinical recovery. At each visit, routine blood exams and medical visits will be conducted, along with several assessments via questionnaires, including the short version of the post COVID-19 WHO Case Report Form (WHO CRF) for collection of symptoms and newly emerged complaints after COVID-19, the Fatigue Numerical Rating Scale, the Medical Research Council (MRC) dyspnoea scale, the 5-level EQ-5D test (EQ5D-5L), the 12-item WHO Disability Assessment Schedule (WHODAS), the Montreal Cognitive Assessment (MOCA), the Hospital Anxiety and Depression Scale (HADS-A/D), and a screening tool named PCL-5 for Post-Traumatic Stress Disorder (PTSD). If patients are unable to attend the post-COVID-19 clinic, the questionnaires will be able to be completed through a phone interview. All questionnaires will be standardized and available in multiple languages (Fig. 1).

Further instrumental diagnostic evaluations such as diffusing capacity of lung carbon monoxide (DLCO), spirometry, lung computed tomography (CT) scans, pneumological evaluation, echocardiography, cardiological evaluation, neurological evaluation, rehabilitation medicine specialist examination, and psychological evaluation will be conducted as necessary.

Pulmonary symptoms are common after the acute phase, thus patients undergo the MRC dyspnoea scale and oxygen saturation measurement at each post-COVID visit. Further evaluations such as chest CT scans, diffusing capacity of lung carbon monoxide (DLCO), spirometry, and a complete pneumological evaluation will be performed if oxygen saturation is < 95% or MRC dyspnoea scale grade is 2–5.

Patients who recovered from acute COVID-19 disease could present a higher risk of cardiac diseases, including heart failure, myocardial infarction, and arrhythmia in the mid- and long-term [18]. During the scheduled post-COVID visits, patients undergo a complete medical examination, including heart rate and blood pressure measurement, and fill in the MRC dyspnoea scale. Further evaluations such as an electrocardiogram, a cardiologic visit, and an echocardiography will be performed as necessary.

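### The attendance weights correct selection on measured characteristics only, not attendance driven by ongoing symptoms, so the stated bias correction needs a limit and a sensitivity analysis

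*Protocol article*

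**What the plan says.** The Data analysis section of the protocol article expects that not every patient will attend the post-COVID visit, and warns that this may cause collider bias in exposure effects. Its remedy is: "This bias can be addressed for hospitalised patients by using Inverse Probability Weighting through the creation of a pseudo-sample". A multivariable logistic model is to estimate "the probability of COVID-19 hospitalised individuals to be included in the post COVID-19 cohort based on their characteristics (propensity score, PS"), and attenders are weighted by 1/PS. Then: "Weighted logistic regression analyses will then be used to investigate predictors of post COVID-19 condition".

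Three other places bear on this:

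- Possible study strengths and limitations gives the expected reason for loss: "patients without ongoing symptoms may not keep follow-up appointments, leading to losses in follow-up". It adds that statistical methods could handle this bias. The Discussion repeats the idea and names propensity score matching.
- Data collection shows what is on record before any visit: "During the acute phase of COVID-19 disease, data collection involves gathering demographic, clinical, and viro-immunological data".
- Patient assessment and follow-up protocol offers a partial safeguard: "If patients are unable to attend the post-COVID-19 clinic, the questionnaires will be able to be completed through a phone interview".

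**The concern.** The remedy and the named cause of loss do not match. The remedy models attendance on patient characteristics. The cause is the presence or absence of symptoms at follow-up, which is the outcome. Someone never assessed has no recorded outcome, so it cannot be a variable in the attendance model. The article does not list the model's variables. That they are acute-phase data is an inference from Data collection, but a safe one for patients without any visit.

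Risk factors are part of the primary objective, and this weighting is the only analysis step specified against selection bias in them. A reader of the weighted results could take them as corrected for symptom-driven attendance when they are not.

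**Working it through.** The plan gives no figure for attendance by symptom status, so there is none to reproduce. All attendance rates below are assumptions.

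**Inputs from the article (sample-size paragraph).** Risk of post-COVID-19 condition 54%; a 25% relative reduction gives 0.54 × 0.75 = 40.5%. True odds ratio (OR) = (0.405/0.595)/(0.54/0.46) = 0.580.

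**Formula.** Let s(y,x) be the probability of attending with symptom status y (1 = symptomatic) at predictor level x. Among attenders

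OR = true OR × [s(1,1) × s(0,0)] / [s(0,1) × s(1,0)].

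A weight 1/P(attend | x) multiplies the symptomatic and the symptom-free attenders at level x by the same number. That number cancels from the OR. So when the model contains the weighting variables, the weighted and unweighted ORs are equal, biased or not.

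**1. Attendance depends on symptoms alone** (50% symptom-free, 80% symptomatic, at both predictor levels). Factor = (0.8 × 0.5)/(0.5 × 0.8) = 1. OR 0.580: no bias.

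**2. Symptoms and predictor act multiplicatively** (50%/80% against 40%/64%). Factor = (0.64 × 0.5)/(0.40 × 0.8) = 1. OR 0.580: no bias.

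**3. Symptoms and predictor add on the logit scale, without interaction.** Reference level 50%/80%, a symptom-attendance odds ratio of (0.8/0.2)/(0.5/0.5) = 4.

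| Predictor log-OR for attendance | Attendance at x = 1, symptom-free / symptomatic | Factor | OR, weighted and unweighted |
|---|---|---|---|
| +1 | 73.1% / 91.6% | (0.916 × 0.5)/(0.731 × 0.8) = 0.783 | 0.454 |
| -1 | 26.9% / 59.5% | (0.595 × 0.5)/(0.269 × 0.8) = 1.38 | 0.802 |

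**4. Where the weights work.** Add a two-level severity variable L, equally common at both predictor levels, with a log-OR of 1.0 on symptoms. Let attendance depend on predictor and severity only: 30%/80% at x = 0 and 70%/60% at x = 1 (mild/severe). The OR not adjusted for L is 0.599 in truth, 0.460 unweighted and 0.599 weighted. The weights remove the bias completely.

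**5. Both mechanisms together.** Logit attendance = -0.5 + 0.8x + 1.0L - 1.2xL + 1.39y. The unadjusted OR is 0.599 in truth, 0.517 unweighted and 0.551 weighted, so part of the bias goes. Within levels of L the true OR is 0.580; the estimates are 0.454 and 0.646, unchanged by weighting.

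**6. Can the proposed remedy be computed?** Take case 3 with log-OR +1, per patient at x = 1. Symptomatic attenders n1 = 0.405 × 0.9158 = 0.3709; symptom-free attenders n0 = 0.595 × 0.7311 = 0.4350; non-attenders 1 - 0.8059 = 0.1941. Fix the symptom-attendance odds ratio at 4 and require the weights to sum to the full group. Then exp(-a) = 0.1941/(0.4350 + 0.3709/4) = 0.368, so the intercept is a = 1, the value that generated the data. The weights are 1.368 (symptom-free) and 1.092 (symptomatic). They give back 0.4350 × 1.368 = 0.595 and 0.3709 × 1.092 = 0.405, the true risks. The analysis needs only the attender and non-attender counts that the planned weights already use.

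**The case against.** A fair defence has four parts.

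- **Selection on the outcome alone does not bias logistic odds ratios**, as in case-control sampling (cases 1 and 2). The limitations section says only that symptom-free patients may stay away; it states no dependence on a predictor. This stands. However, the plan itself speaks of collider bias and models attendance on characteristics, which presumes that these matter too. Once symptoms also matter, plain additivity on the logit scale is enough to shift the OR (case 3).
- **The weights are not redundant.** A reader might infer that the weighted odds ratios simply keep all the bias of the unweighted ones. The documents do not support that. The plan includes univariable models and does not say that every weighting variable enters the outcome model, and there the weights help (cases 4 and 5). The variant hypothesis runs partly through disease severity, so adjusting for severity would take out part of the effect sought. Weighting is then the suitable tool for selection on severity.
- **Large distortions need strong assumptions.** A reader might infer that effects could reverse. With 80% attendance among symptomatic patients, and 70% (exposed) against 40% (unexposed) among symptom-free ones, a true OR of 1.50 becomes 1.50 × (0.8 × 0.4)/(0.7 × 0.8) = 0.86. With 60% against 45% it becomes 1.50 × (0.8 × 0.45)/(0.6 × 0.8) = 1.13. The arithmetic is right, but no such rates stand in the documents.
- **The risk is disclosed and partly mitigated** by telephone questionnaires and telehealth. These can reduce loss but do not correct for what remains.

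A condensed article may also leave sensitivity analyses to fuller documents. That is fair as to detail. The statement that the bias can be addressed, however, is in the text and goes further than the method does.

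**Conclusion.** The point holds in a limited form. Weights based on characteristics correct selection on those characteristics. They cannot correct attendance that still depends on symptoms once the characteristics are accounted for, which is the kind of loss that the article itself names.

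The consequence is conditional. There is no bias in the odds ratios under symptom-only or multiplicative attendance. Under joint, non-multiplicative dependence, the odds ratios conditional on the weighting variables are biased by the same amount weighted or unweighted. In the illustration a true 0.580 reads 0.454 to 0.802 for predictor log-odds ratios of +1 to -1. The direction and size rest wholly on assumed attendance rates; the true ones are unknown. This calls for a limit on the claim and a check of robustness. It is not a reason to abandon the weighting.

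**What to change.** In the Data analysis section:

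1. State that the weights correct only for selection on measured characteristics. Keep them.
2. For the main predictors, add a sensitivity analysis with weights 1/P(attend | characteristics, outcome). Fix the symptom-attendance odds ratio over a stated range, for example 1 to 4. Hold it equal across predictor levels first, then allow a limited difference with a stated justification. Without such a limit nearly any predictor could be made to fail.
3. For each of these predictors, report the value at which its direction or significance is lost.

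Like the planned weights, this applies to hospitalised patients. The cost is one sentence and some extra analysis on existing data. The downside is that some predictors may have to be reported as not robust.
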